### Proposed sample size

The twenty-four participating hospitals were initially selected by calculating anticipated hospital specific effect sizes based on assuming that the effect of intervention would be proportional to baseline admission rates taking into account hospital-specific frequencies of disease episodes. Hospitals are to be randomized to one of three intervention arms, eight hospitals per arm, after stratification on baseline frequency of disease episodes. The power of our study depends on the anticipated change in mean hospital days as shown in Figure 1, which provides power estimates plotted against percentage decrease based on examining hospital stays over the three baseline and three post-intervention years. (Appendix A – Details of calculations) A Bonferroni correction for the two comparisons of intermediate and high intensity intervention against low intensity intervention has been included. The estimated power (overall alpha = .05) to detect a 25% change is 0.80 for each comparison.

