### Proposed duration of treatment period

Detailed planning for the intervention strategies will take place between February and July 2003. We will initiate each of the interventions in August, 2003 and conclude them in March, 2004.

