### Duration of the baseline and follow-up periods

#### Utilization and adverse outcome data obtained from the administrative datasets

We have extracted data from administrative databases from April 1^st^, 1994 to March 31^st^, 2000, providing six years of data. In summer 2006, we will again extract data from administrative databases from April 1^st^, 2000 to March 31^st^, 2006. Extraction of data across these time periods will allow us to extend the baseline utilization rates from six to nine years. Most importantly, this will ensure no significant changes occur just prior to the study interventions. Extraction of data through March 31^st^, 2006 will provide utilization data for the intervention and two follow-up years.

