### Proposed analyses

The principal analysis will examine hospital stays arising from individual disease episodes over the six-year baseline and study period. We will apply a linear mixed model (Laird-Ware approach) incorporating random effects for hospital, year within hospital, as well as fixed effects for intervention and year. We will also pursue a more detailed explanatory analysis incorporating individual subject characteristics (age, sex) as well as random effects for admission and discharge physician. Additionally we will develop similar models for length of stay restricting to disease episodes leading to admissions, and mixed effects logistic regression model for admissions. Secondary analyses relating to steroid use and *Telephone OutPatient (TOP) *scores will follow a similar format. The examination of day 1- 3 *TOP *scores will require augmenting the basic model framework to include random subject effects and a serially correlated (within subject) residual error structure. No subgroup analyses are planned.

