#### Calculation of societal costs

Total societal costs (the sum of payer and non-payer costs) for each hospital will be calculated for the 9 baseline years, the one-year of intervention, and the two years of follow-up. Given the year-to-year variability in the incidence of croup, the total societal costs for each year will be adjusted for disease incidence (total costs per year divided by the number of episodes of croup diagnosed that year by those physicians assigned to the hospital). An average cost per year for the baseline period will be calculated. Statistical assessment of whether or not costs differ between the three intervention groups will be calculated by the Laird-Ware model with baseline costs as the covariate. (This type of analysis will allow us to simultaneously compare costs at three time points (the intervention year and two years of follow-up), while adjusting for the baseline cost)

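### The 0.80 power counts three post-intervention years, but the calendar supplies a roll-out year plus two, and the primary-analysis window is not consistently fixed

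*Protocol article*

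**What the plan says.** *Proposed sample size* fixes the design ("Hospitals are to be randomized to one of three intervention arms, eight hospitals per arm") and the multiplicity rule ("A Bonferroni correction for the two comparisons of intermediate and high intensity intervention against low intensity intervention has been included"). It then says that the power estimates are "plotted against percentage decrease based on examining hospital stays over the three baseline and three post-intervention years" and concludes: "The estimated power (overall alpha = .05) to detect a 25% change is 0.80 for each comparison".

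Four other sections bear on which years those are:

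- *Proposed duration of treatment period*: "We will initiate each of the interventions in August, 2003 and conclude them in March, 2004".
- *Utilization and adverse outcome data obtained from the administrative datasets*: extraction to 31 March 2006 "will provide utilization data for the intervention and two follow-up years". The same section extends the available baseline from six years (April 1994 to March 2000) to nine (to March 2003).
- *Proposed analyses*: "The principal analysis will examine hospital stays arising from individual disease episodes over the six-year baseline and study period".
- *Calculation of societal costs*: costs "will be calculated for the 9 baseline years, the one-year of intervention, and the two years of follow-up".

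**The concern.** The power statement and the calendar count the years after the intervention differently. Three fiscal years lie between the end of the longest baseline (March 2003) and the end of data (March 2006). The protocol itself divides them into one intervention year and two follow-up years, whereas the power statement treats all three as post-intervention. Nothing in the text shown says that a partial effect in the roll-out year was allowed for.

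The sentence that defines the principal analysis does not settle the matter. Its six years may be a six-year baseline followed by the study period, or six years covering baseline and study together. The model has a fixed effect for intervention, but the protocol does not say whether 2003–04 counts as exposed.

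Two things are at stake. First, coding the roll-out year as fully exposed would pull the estimated effect towards zero, because part of that year precedes the interventions and the rest falls while they are being delivered. Second, the 0.80 is the trial's only stated justification for 24 hospitals, and a reader cannot tell which window it describes.

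**Working it through.** **Calendar, in fiscal years (April to March)**

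| Period | Status from the protocol's dates | Years |
|---|---|---|
| April 1994 – March 2000 | first extraction | 6 |
| April 2000 – March 2003 | second extraction, before intervention | 3 |
| April 2003 – March 2004 | roll-out: 4 months before any intervention, 8 months of delivery | 1 |
| April 2004 – March 2006 | after delivery has ended | 2 |

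The 3+3 of the power statement therefore fits only if the roll-out year is counted as a full post-intervention year.

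**Can the 0.80 be reproduced?** No. The text gives no mean, between-hospital SD or year-within-hospital SD, and Figure 1 and the appendix with the calculations are not shown. The figure can be neither confirmed nor refuted, so it is taken as correct for 3+3 and used as the calibration point.

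**Calibration.** The inputs from *Proposed sample size* are 8 hospitals per arm, a 25% change, power 0.80, and overall alpha 0.05 split over two comparisons, so 0.025 each. Two-sided testing is assumed, as the sidedness is not stated.

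- z(0.9875) + z(0.80) = 2.241 + 0.842 = 3.083.
- The implied SD of the hospital-level change is 0.25 × √(8/2) / 3.083 = 0.162, or 16.2% of the mean. With that SD, 8 per arm returns 0.80.

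**Rescaling.** With b baseline and p post years, independent years and a simple change score, the variance is proportional to 1/b + 1/p. With e the average effect as a fraction of the full 25%:

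Power = Φ( 3.083 × e / √[(1/b + 1/p) / (1/3 + 1/3)] − 2.241 )

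*Roll-out year excluded (p = 2, e = 1):*

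- 3+2: (1/3 + 1/2)/(2/3) = 1.25; √1.25 = 1.118; 3.083/1.118 − 2.241 = 0.516; power 0.70.
- 6+2: (1/6 + 1/2)/(2/3) = 1; power 0.80, unchanged.
- 9+2: (1/9 + 1/2)/(2/3) = 0.917; √0.917 = 0.957; 3.083/0.957 − 2.241 ≈ 0.98; power 0.84.

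*Roll-out year counted as fully exposed on 3+3.* The share f of the full effect that it carries is an assumption. Then e = (2 + f)/3.

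| f | Average effect | Power, 3+3 |
|---|---|---|
| 1 | 25.0% | 0.80 |
| 0.75 | 22.9% | 0.72 |
| 0.5 | 20.8% | 0.63 |
| 0 | 16.7% | 0.43 |

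With f = 0.5 and a longer baseline the same formula gives 0.77 (6+3) and 0.82 (9+3).

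**Sensitivity to the variance model** (roll-out year excluded, again calibrated to 0.80 at 3+3):

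| Variance model | 3+2 | 6+2 | 9+2 |
|---|---|---|---|
| Independent years, change score | 0.70 | 0.80 | 0.84 |
| 25% to 75% of the change variance not reduced by adding years | 0.72–0.77 | 0.80 | 0.81–0.83 |
| Random hospital intercept, ICC 0.2 to 0.9 | 0.66–0.70 | 0.69–0.79 | 0.71–0.83 |

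The 3+2 window is below 0.80 in every row. Whether six or nine baseline years make up the loss depends on the variance structure.

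**The case against.** The strongest reply is that much of the apparent conflict is wording.

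- **Six years.** The phrase in *Proposed analyses* may mean six years in total. That would equal 3+3 and match the second extraction exactly (April 2000 to March 2006). This stands: a reader might infer a flat three-versus-six-versus-nine contradiction, but the six is ambiguous, not shown to conflict.
- **Nine years.** The nine describe how far the data reach and the window of the cost analysis. Holding nine years and powering on three is not in itself contradictory. This also stands. Nor does the extraction section rank 2000–2003 as the most important years; its emphasis is on checking that nothing changed shortly before the interventions.
- **Loose wording for years since the start.** Counting from the start of the intervention is a legitimate choice, and the cost analysis does include the intervention year. But the protocol elsewhere separates one intervention year from two follow-up years, and the power statement does not.
- **Little dilution.** By the protocol's own epidemiology, April to July lies outside both croup peaks, so calendar months overstate the unexposed episodes. That is fair, and it is one reason why the half effect is only an assumption. Exposure during delivery from August to March would still be partial.
- **Masking.** The statistician receives encrypted hospital and intervention labels. This limits a choice of years by direction of effect. However, the data arrive already grouped by arm, so differences between arms are visible.

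A reader might also infer that the trial is underpowered or that the 0.80 is miscalculated. The documents support neither. No variance inputs are shown, the simple model returns 0.80 for 6+2 and 0.84 for 9+2, and the unseen appendix may have allowed for partial exposure.

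**Conclusion.** The point holds in limited form. The stated power is tied to three post-intervention years, while the protocol's dates give one roll-out year and two years fully after it. The baseline for the primary analysis is not consistently fixed either.

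Conditional on 0.80 being right for 3+3, and on two-sided 0.025, independent years and change-score scaling, the choice of window moves power between about 0.70 (3+2) and 0.84 (9+2) with the roll-out year excluded. It is about 0.63 on 3+3 if that year is coded as fully exposed but carries half the effect. The change-score scaling simplifies the planned mixed model. These figures show how far the headline number depends on the window; they are not a replacement power.

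**What to change.** 1. In *Proposed sample size* and *Proposed analyses*, state the same baseline window by calendar date. It should include April 2000 to March 2003: either those three years, or all nine from April 1994. Choose before the summer 2006 extraction.
2. Define the post period as April 2004 to March 2006.
3. Exclude April 2003 to March 2004 from the primary contrast, or give it its own transition term. Add a sensitivity analysis that includes it.
4. Recalculate and restate the power for that window with the variance inputs already used.

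The cost is some wording and one recalculation. The stated power may fall, to about 0.70 with a three-year baseline under the scaling above, and one partly exposed year leaves the primary contrast. No additional data are needed, since the planned extraction already covers all these years.

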#### Primary objective

To determine which of the three intervention strategies are most effective at lowering the rate of hospital days per 1,000 disease episodes. The null hypothesis is that none of the intervention strategies reduce hospital utilization rates from baseline. The alternate hypothesis is that the intervention strategies will have a graded degree of effect on hospitalization rates, with the low intensity intervention having minimal to no effect, the intermediate intensity intervention having moderate but significant effect, and the high intensity intervention having the greatest effect.

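### The Bonferroni rule for the two comparisons with low intensity gives away power that Holm would keep at the same overall alpha, and the power statement does not say which arm's effect the 25% is

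*Protocol article*

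**What the plan says.** In the Protocol article, Proposed sample size fixes the allocation: "Hospitals are to be randomized to one of three intervention arms, eight hospitals per arm". It states the multiplicity rule: "A Bonferroni correction for the two comparisons of intermediate and high intensity intervention against low intensity intervention has been included". It then gives one power figure: "The estimated power (overall alpha = .05) to detect a 25% change is 0.80 for each comparison". The same section says that Figure 1 "provides power estimates plotted against percentage decrease based on examining hospital stays over the three baseline and three post-intervention years", and it refers to "Appendix A – Details of calculations" for the inputs. Neither the figure nor the appendix is in the text at hand.

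The Primary objective states a graded alternative: "the low intensity intervention having minimal to no effect", then "the intermediate intensity intervention having moderate but significant effect, and the high intensity intervention having the greatest effect". It attaches no percentage to any arm.

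Proposed analyses describes the mixed model but names no multiplicity procedure, so Proposed sample size is the only place where the article states one.

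**The concern.** There are two linked issues.

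First, one effect size and one power serve two comparisons that the trial's own hypothesis expects to differ. The text does not say whether 25% is the effect expected for intermediate, for high, or simply a benchmark. If it belongs to the high arm, the intermediate comparison has less than 0.80 under the stated hypothesis.

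Second, single-step Bonferroni holds the intermediate test at 0.025 even after high v low has been rejected. A step-down rule releases that test to 0.05 at no cost in familywise error.

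At stake is the intermediate strategy. The economic hypothesis (Aim and objectives, Economic analysis) expects it to use the fewest resources. A missed intermediate effect could be read as showing that only the high intensity strategy works. With eight hospitals per arm, power that comes from the testing rule is much cheaper than power from more clusters.

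**Working it through.** **Inputs from the Protocol article.** Overall alpha 0.05; two comparisons with low intensity; Bonferroni, so 0.025 each; power 0.80 at 25%; 8:8:8 hospitals.

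**Assumptions.** Two-sided tests (sidedness is not stated). Normal test statistics. Correlation 0.5 between the two statistics, because equal arms share the low arm. Noncentrality linear in the percentage reduction. All effects other than 25% are assumed.

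**1. Calibrate to the stated power.** The variance inputs are not shown, so 0.80 cannot be rebuilt independently; it is used as the anchor. The noncentrality at 25% is z(0.9875) + z(0.80) = 2.241 + 0.842 = 3.083. The implied standard error is 25/3.083 = 8.11 percentage points. By construction, Φ(3.083 − 2.241) = 0.80.

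**2. Intermediate v low under Bonferroni.** Power = Φ(3.083 × effect/25 − 2.241).
- 20%: Φ(2.466 − 2.241) = Φ(0.225) = 0.59
- 15%: Φ(1.850 − 2.241) = Φ(−0.391) = 0.35
- 12.5%: Φ(1.542 − 2.241) = Φ(−0.700) = 0.24

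**3. Holm.** The smaller p is tested at 0.025 and, if rejected, the other at 0.05. Intermediate v low is rejected if Z_I > 2.241, or if 1.960 < Z_I ≤ 2.241 and Z_H > 2.241. Its power is therefore the Bonferroni power plus the bivariate normal probability of the second event, and it cannot be lower.

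| True effect, high / intermediate | Int. v low, Bonferroni | Int. v low, Holm | Gain (points) | Both significant, Bonferroni | Both significant, Holm |
|---|---|---|---|---|---|
| 25% / 25% | 0.800 | 0.846 | 4.6 | 0.687 | 0.778 |
| 25% / 20% | 0.589 | 0.670 | 8.1 | 0.529 | 0.637 |
| 25% / 15% | 0.348 | 0.442 | 9.4 | 0.325 | 0.430 |
| 25% / 12.5% | 0.242 | 0.328 | 8.6 | 0.230 | 0.323 |
| 35% / 25% | 0.800 | 0.867 | 6.7 | 0.794 | 0.864 |
| 35% / 17.5% | 0.467 | 0.578 | 11.1 | 0.465 | 0.577 |

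In the 35% / 25% row, high v low has power 0.981 under Bonferroni. That pair is graded, and both comparisons have at least 0.80.

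**4. Error control.** If both nulls are true, Holm makes a false rejection only when the smaller p is at or below 0.025, exactly as Bonferroni does. Simulation gave 0.046 for both rules. If only one null is true, it is never tested above 0.05.

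**5. Sensitivity.**
- t distribution with 14 or 21 df, recalibrated to 0.80: Bonferroni power for intermediate is 0.59 at 20% and 0.24 at 12.5%, unchanged to two decimals.
- Effect on the log scale: 0.56 and 0.21.
- One-sided tests: noncentrality 1.960 + 0.842 = 2.802, so at 20% Φ(2.241 − 1.960) = 0.61 and at 12.5% Φ(1.401 − 1.960) = 0.29.

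**The case against.** The strongest reply is that nothing stated is wrong. The sample-size sentence is conditional: it gives the power if the change is 25%, and refers the reader to Figure 1 for other decreases. Bonferroni is valid. It appears only as part of the power calculation, and sizing with it does not bar a sharper rule at analysis. Much of this stands. The 0.80 is a correct kind of statement, and Figure 1 may already show the lower power at smaller decreases. A per-comparison curve would still not say where intermediate is expected to lie, nor recover what single-step testing gives up. And since the article states only one multiplicity rule, that is the rule to amend.

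A reader might infer that the graded alternative makes 0.80 for both comparisons impossible. The documents do not support that. The Primary objective gives no percentages, and the 25% is not assigned to the high arm. Intermediate at 25% with high at 35% fits the hypothesis and keeps at least 0.80 for each.

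A reader might also infer that the trial is likely to miss a real intermediate effect. That depends on the assumed effect: at 20%, Bonferroni power is 0.59, so detection is more likely than not. Nor does the article set a success rule that needs both comparisons significant; the joint figures are supplementary.

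**Conclusion.** The point holds as an efficiency and clarity improvement.

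- The stated 0.80 applies to any comparison whose true effect is at least 25%. If 25% is the effect of the high arm, power for a smaller intermediate effect is below that: 0.59 at 20%, 0.24 at 12.5%.
- Replacing Bonferroni with Holm adds about 5 to 11 points to intermediate v low: about 5 if both effects are 25%, 8 to 9 with high at 25% and intermediate at 12.5–20%, and 11 with high at 35% and intermediate at 17.5%.
- Most of any shortfall from 0.80 comes from the smaller effect, not from the testing rule. At 12.5% the shortfall is 0.80 − 0.242 = 0.558, and Holm recovers 0.086 of it.

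These figures rest on the assumptions listed above and on taking the stated 0.80 as correct. That Holm never rejects less than Bonferroni does not depend on them.

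**What to change.** In Proposed sample size, and in the primary analysis, replace Bonferroni with Holm for the two comparisons with low intensity: test the smaller p-value at 0.025 and, if it is rejected, the other at 0.05. In the power statement, say which arm the 25% refers to, and give the power for the other arm at the effect expected there. The power for both comparisons to be significant could be added.

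The cost is two sentences and a recalculation. Hospitals, data and overall alpha are unchanged. The stated power for one arm may look less favourable. Holm has no simple matching simultaneous confidence intervals, but Bonferroni intervals can still be shown beside the Holm tests, with a note that the two may occasionally disagree.

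### The primary objective ranks high above intermediate intensity, but the stated alpha correction and power cover only the two comparisons with low intensity

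*Protocol article*

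**What the plan says.** The Primary objective section sets the question: "To determine which of the three intervention strategies are most effective at lowering the rate of hospital days per 1,000 disease episodes". Its alternative hypothesis is an ordering, in which "the intervention strategies will have a graded degree of effect on hospitalization rates", with "the intermediate intensity intervention having moderate but significant effect, and the high intensity intervention having the greatest effect". Its null hypothesis is framed differently, as change over time within arms: "The null hypothesis is that none of the intervention strategies reduce hospital utilization rates from baseline".

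The Proposed sample size section describes the design as "Hospitals are to be randomized to one of three intervention arms, eight hospitals per arm, after stratification on baseline frequency of disease episodes". On multiplicity it states: "A Bonferroni correction for the two comparisons of intermediate and high intensity intervention against low intensity intervention has been included". On power it states: "The estimated power (overall alpha = .05) to detect a 25% change is 0.80 for each comparison".

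The Low intensity intervention section makes that arm the control. The Proposed analyses section fits a linear mixed model with a fixed effect for intervention, and names no contrast, trend test or order of testing.

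**The concern.** To call one of three strategies the most effective, or to show that high intensity has the largest effect, high must be compared with intermediate. Two comparisons against a common control do not do this. Both can reject while the order of the two active arms stays open.

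All of the alpha (2 × 0.025 = 0.05) is given to the comparisons with low. A high versus intermediate test added afterwards would fall outside the error control, and no power is stated for it.

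The contrast matters in the article's own terms. According to the Abstract and the High intensity intervention section, high adds local opinion leaders and a local consensus process to the intermediate package. The section on systematic reviews reports mixed evidence for opinion leaders. Only high versus intermediate isolates what those additions contribute. If both active arms beat mailing, the objective still asks for a winner, and the risk is that one is named from point estimates based on eight hospitals per arm.

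**Working it through.** **Inputs from the Proposed sample size section.** Three arms of 8 hospitals; overall alpha 0.05 split over two comparisons, so 0.025 each; power 0.80 for a 25% change in each.

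**Assumptions.** Two-sided normal test; the same standard error (SE) for all three pairwise contrasts, since the arms are equal in size; effects on an additive scale of percentage points of decrease. The text at hand gives no variance, intracluster correlation or sidedness. The power figure and the appendix are not shown, so the stated 0.80 cannot be reproduced independently and is taken as given.

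**Step 1: implied precision.**
SE = 25 / (z₀.₉₈₇₅ + z₀.₈₀) = 25 / (2.241 + 0.842) = 25 / 3.083 = 8.11 points.
This corresponds to a hospital-level SD of 8.11 / √(2/8) = 16.2 points. Putting it back returns power 0.80 at 25 points and alpha 0.025.

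**Step 2: power for high versus intermediate.** Power = Φ(d/SE − z), with z = 1.960 at alpha 0.05 and 2.241 at alpha 0.025. The gaps d are assumed.

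| Gap d (points) | Power at 0.05 | Power at 0.025 |
|---|---|---|
| 10 | Φ(1.233 − 1.960) = 0.23 | 0.16 |
| 12.5 | Φ(1.541 − 1.960) = 0.34 | 0.24 |
| 15 | 0.46 | 0.35 |
| 20 | 0.69 | 0.59 |
| 25 | 0.87 | 0.80 |

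With a t reference on 14 or 21 degrees of freedom, again calibrated to 0.80 at 25 points, 12.5 points at 0.025 still gives 0.24. A 95% confidence interval for high versus intermediate would have a half-width of about 1.96 × 8.11 = 15.9 points. To detect 12.5 points with power 0.80 at 0.025 would take about 32 hospitals per arm: half the gap needs four times the 8.

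**Step 3: adding a third test without a plan.** By simulation under no difference between arms, the two planned tests at 0.025 have a family error of 0.046. Adding high versus intermediate at 0.025 raises it to 0.064; adding it at 0.05 raises it to 0.085.

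**Step 4: a valid three-arm procedure.** There are three pairwise null hypotheses, and if any two are true the third is true as well. The only intersection to protect is therefore the hypothesis that all arms are equal. The planned Bonferroni pair is a valid test of that hypothesis at 0.05. If it rejects (either comparison with low has p below 0.025), each pair can be tested at 0.05 by the closed testing principle. If exactly one pairwise null is true, only one false rejection is possible and its probability is at most 0.05.

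Simulated results with SE 8.11 (effects in points for low/intermediate/high):

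| Scenario | Contrast | Planned Bonferroni | Two-step closed test |
|---|---|---|---|
| 0/0/0 | any false rejection | 0.046 | 0.046 |
| 0/25/25 | each versus low | 0.80 | 0.85 |
| 0/12.5/25 | intermediate versus low | 0.24 | 0.33 |
| 0/12.5/25 | high versus low | 0.80 | 0.81 |
| 0/12.5/25 | high versus intermediate | no test | 0.32 |

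Anything that rejects at 0.025 under the present plan passes the first step and is also below 0.05, so neither comparison with low can lose power.

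**The case against.** **The contrast can still be estimated.** A reader might infer that high versus intermediate cannot be answered at all. The article does not support that. One mixed model is fitted to all 24 hospitals, and it yields this contrast with a confidence interval at about the same precision as the planned ones. A gap near 25 points would be detectable. This stands, and it limits the point to confirmatory status and power.

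**The sentence comes from a power paragraph.** It does not say that no other test will be run, and contrast lists are often left to an analysis plan. The first part stands: an express exclusion should not be read into it. But the article does state a family of two comparisons that exhausts alpha, and it states an objective that this family does not serve. That is a mismatch between two stated items, not a detail left out. The appendix cited as "Appendix A – Details of calculations" may hold variance inputs, but it would not turn a correction for two comparisons into one for three.

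**Powering against control is legitimate.** This is true, and Bonferroni on two tests is valid and conservative. A reader might take its use as an error; it is not one. The difficulty lies in pairing it with an objective that ranks the active arms.

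**The main policy question.** A reader might call high versus intermediate the trial's central question. The article does not say so. The economic alternative hypothesis does expect intermediate to use fewer resources than high, but that is a separate cost comparison.

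**The gains against low do not need a third contrast.** This is correct: Holm's method on the two planned comparisons gives about 0.845 each under 0/25/25 and 0.328 and 0.804 under 0/12.5/25. What the three-arm procedure adds is a valid high versus intermediate test, and its power is low.

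**Conclusion.** The point holds in limited form. The objective and the graded alternative need high versus intermediate; the stated correction and power cover only the two comparisons with low. High versus intermediate can be estimated, but it has no alpha-controlled test and no stated power.

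On the implied SE of about 8.1 points, power at 0.05 is about 0.23 for a 10-point gap and 0.34 for 12.5 points, so a graded step of that size would usually not be shown. These figures rest on the assumptions listed with the calculation. The gaps are illustrative, since the article gives no size for the gradient. The mismatch itself does not depend on them.

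This should be corrected because it governs what the trial may claim if both active arms beat mailing. It does not undermine the two planned comparisons.

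**What to change.** 1. Keep the two comparisons with low at 0.025 each as the first step. If either rejects, test all three pairwise contrasts at 0.05, two-sided. State that this is a closed test and that it is valid because there are exactly three arms.
2. State the power for high versus intermediate over a range of gaps, from the variance inputs behind the sample size, and say that it is low.
3. Reword the objective: without a significant high versus intermediate result, the conclusion is limited to better than mailing, and the high versus intermediate estimate is reported with its confidence interval.
4. Reword the null hypothesis as differences between arms, so that it matches the contrasts tested.

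The cost is wording only, with no added hospitals or data and no loss of power for either comparison with low. A third Bonferroni comparison at 0.05/3 would also be valid. It would, however, lower power at 25 points from 0.80 to about 0.755 and raise the difference detectable with 80% power from 25.0 to 26.2 points. The least change would be to adopt items 3 and 4 alone and label high versus intermediate as estimation.
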